### Statistical Analysis

We will first check whether or not the randomization was successful by comparing the two groups for all baseline variables with *t* tests for continuous data or chi-square tests for dichotomous data. We will also check for differences between study dropouts and those who remain in the study at 3 months. The primary analyses will be based on the intention-to-treat principle. Sensitivity analyses will be performed only with those participants that filled out the pre- and posttest questionnaires (ie, completers). Missing data handling will depend on the amount and pattern of missing data, selecting the most appropriate technique. We will use the generalized estimating equation to examine the association between changes in stress scores (ie, PSS scores) and treatment arms (ie, iSupport vs waiting list). We will correct for baseline scores if they are not equally distributed. We will examine the influence of age, gender, and relationship (ie, spouses vs other relationship) on the outcomes. These analyses will be repeated for burden, anxiety and depression, sense of competence, self-efficacy, and mastery. Next, we will express the between-group, posttest, effect sizes for the different outcomes using Cohen *d*. Cohen *d* is the difference between the two posttest means divided by the pooled standard deviation. An effect size of 0.8 is considered to be large, an effect size of 0.5 is considered to be moderate, and an effect size of 0.2 is considered to be small.

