### Randomization and Blinding

A randomization schedule with a 1:1 allocation ratio will be made with a computerized random number generator using variable block sizes of two and four by an independent researcher. We will stratify for gender and for the type of relationship between the carer and the person with dementia (ie, partner or other). After every inclusion, the same independent researcher will reveal the next randomization outcome so that allocation is concealed. Participants will be informed about the randomization outcome by email.

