	**Treatment adherence, usage, and satisfaction**						
		SUS^p^	Usability	10	N/A	x	N/A
		Postlesson questions	Satisfaction	2 per lesson	N/A	x	N/A
		Analysis of platform data	Intervention usage	N/A	N/A	x	N/A

^a^T0: baseline assessment.

^b^T1: 3-month follow-up assessment.

^c^T2: 6-month follow-up assessment.

^d^Demographic data of carers: age, gender, marital status, number of children, children living at home, relationship with the person with dementia, level of education, months of caregiving, and average days per week providing care. Demographic data of persons with dementia: age, gender, marital status, living situation, and diagnosis.

^e^The questionnaire is included at the questionnaire battery for the different time points (T0, T1, T2), in opposition to N/A.

^f^Not applicable.

^g^AD8: Ascertain Dementia 8-item informant questionnaire.

^h^PSS: Perceived Stress Scale.

^i^CES-D: Centre for Epidemiological Studies Depression scale.

^j^HADS-A: Hospital Anxiety and Depression Scale-Anxiety subscale.

^k^ZBI: Zarit Burden Interview.

^l^PMS: Pearlin Mastery Scale.

^m^RIS: relational self-efficacy, instrumental self-efficacy, and self-soothing efficacy.

^n^SSCQ: Short Sense of Competence Questionnaire.

^o^ADQ: Approaches to Dementia Questionnaire.

^p^SUS: System Usability Scale.

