### Sample Size

Perceived stress is our primary outcome measure and is used for the power calculation. Based on the results of a previous study about an online intervention for carers [39], we expect an effect size (Cohen *d*) of 0.40. Assuming an alpha of .05 and a statistical power (1-beta) of .80 in a two-tailed test, we will need 100 respondents in each of the conditions, resulting in a total of 200 participants. Calculation of the sample size was carried out with G*Power 3.1.9.2 (Heinrich-Heine-Universität Düsseldorf) [40].

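### Baseline significance tests are used to judge whether randomization succeeded, although chance differences are expected under sound allocation and no alpha or failure threshold is stated

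*Protocol article*

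**What the plan says.** The protocol article's Statistical Analysis section opens with a check on the allocation: "We will first check whether or not the randomization was successful by comparing the two groups for all baseline variables with *t* tests". Chi-square tests are named for dichotomous variables. The section gives no significance level for these tests, no allowance for their number, and no count or size of difference that would mean failure. It then makes correction for baseline scores conditional on their turning out unevenly distributed between the arms.

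Randomization and Blinding describes a computer-generated 1:1 schedule in blocks of two and four, prepared by an independent researcher. On stratification: "We will stratify for gender and for the type of relationship between the carer and the person with dementia". On concealment: "After every inclusion, the same independent researcher will reveal the next randomization outcome so that allocation is concealed". Under Recruitment of Participants and Study Procedure, only people who have completed the full baseline battery are randomized.

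The baseline variables are set out in Table 2 and its footnote d, which begins: "Demographic data of carers: age, gender, marital status, number of children, children living at home, relationship with the person with dementia, level of education".

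**The concern.** The sentence draws a verdict on the validity of the trial from p values. If the described procedure was followed, the null hypothesis of every baseline test is true by design, so a small p value is a chance finding. Whether the procedure was followed is a question about process, which baseline p values address only indirectly.

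At stake is the wording of the trial report. One or two chance differences could be presented as a sign that randomization did not work, weakening the causal reading of the iSupport comparison without good reason. With no criterion given, whoever reads the table decides what counts as success.

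**Working it through.** **Stated figures.** The article gives no figure for the baseline tests. The nearest are in Sample Size: "Assuming an alpha of .05 and a statistical power (1-beta) of .80 in a two-tailed test", with Cohen d 0.40 and 100 per arm. That calculation reproduces: the t-based solution is 99.08 per arm, rounded up to 100, with power 0.804. The .05 there belongs to the power calculation, so .05 per baseline test is my assumption.

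**Number of variables.**
- Footnote d names 9 carer and 5 person-with-dementia variables, 14 in all. Removing the two stratification factors leaves 12.
- Ten scores are taken at baseline: the one-item burden scale, AD8, PSS, CES-D, HADS-A, ZBI, PMS, RIS, SSCQ and ADQ.
- Total: 12 + 10 = 22.
- The demographic list at the end of Secondary Outcomes has 7 + 5 = 12 variables, giving 12 - 2 + 10 = 20.
- The Table 2 row gives 15 sociodemographic items, so 15 - 2 + 10 = 23, or 25 if the three RIS subscales are tested separately.

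**Chance of at least one p < .05 under sound allocation, independent tests:** 1 - 0.95^k.
- k = 20: 64.2%
- k = 22: 67.6%
- k = 23: 69.3%
- k = 25: 72.3%

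The expected number of significant results is 0.05 × 22 = 1.1.

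**Allowing for correlation.** The variables are not independent; for instance, Secondary Outcomes says that five of the seven SSCQ items are already in the ZBI. Simulated trials with 100 per arm and 22 variables, all treated as continuous, gave the following. The correlations are assumed.

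| r among scales | r among other variables | at least one flag |
|---|---|---|
| 0 | 0 | 68% |
| .3 | .1 | 63% |
| .5 | .2 | 59% |
| .6 | .3 | 54% |
| .7 | .5 | 46% |

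Together with the independent case at k = 25, the range is about 46-72%.

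**Discrimination.** With 22 variables and assumed correlations of .5 among scales and .1 among the others, a shift of s SD moves a test statistic by s × √(100/2).

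| Distortion | at least one flag |
|---|---|
| none | 61% |
| 0.1 SD, all ten scales | 69% |
| 0.2 SD, all ten scales | 86% |
| 0.4 SD, all ten scales | 99.6% |
| 0.1 SD, one scale | 63% |
| 0.2 SD, one scale | 70% |
| 0.4 SD, one scale | 94% |

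A flag is 0.69/0.61 = 1.1 times as likely under the 0.1 SD fault across all scales as under sound allocation. However severe the fault, the ratio cannot exceed 1/0.61 = 1.6. A bare flag therefore says little. Its absence says more: it occurs in 39% of sound trials but only 0.4% of those with 0.4 SD across all scales.

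**Stratification factors.** With blocks of at most four, each of the four strata can be out of balance by at most 2 people, so gender by at most 4. For 100, 140 or 160 women among 200, that worst case gives uncorrected chi-square p values of .57, .54 and .48. In 3,000 simulated stratified trials neither factor was ever significant.

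**The case against.** The strongest objection is that the any-p-below-.05 rule is not in the article. With 22 independent tests, other readings of the same silence give 30% (two or more at .05), 9% (three or more at .05) or 20% (any at .01). This stands, and it is why the percentages are conditional. It does not rescue the sentence, which still promises a verdict without saying how the p values produce one.

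A second objection is circularity: assuming sound allocation in order to call every difference chance presupposes what the check is meant to test. The calculation, however, asks only how often the check would flag a sound trial, and that rate has to be low for a flag to mean much. It is also fair that a significant result on gender or relationship would suggest that the stratified blocks were not applied. Comparison with the schedule answers that directly.

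Third, a reader might infer that the check cannot tell sound from faulty allocation at all. The figures do not support this: a large distortion across many scales would usually be flagged, and a clean result is some evidence against one.

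Fourth, little follows from the check. The only actions the article ties to group differences are correction for baseline scores and possible control for professional support (Inclusion and Exclusion Criteria). This stands and limits the seriousness of the point.

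**Conclusion.** The point holds as a fault in a stated rule. Significance tests on all baseline variables are a poor basis for judging whether randomization succeeded, because about one significant result is expected when it did. At least one would appear in roughly 46-72% of correctly randomized trials. That range assumes .05 per test, any significant difference read as a flag, 20 to 25 variables and the correlations shown. The check discriminates poorly for small distortion or for modest distortion confined to one scale, and a flag cannot by itself be separated from chance.

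Two stronger readings are not supported. One is that the team would usually have to declare randomization unsuccessful; the article sets no threshold that would force this. The other is that the check biases the primary result; it does not directly change the estimate, its standard error or the intention-to-treat analysis. The harm is a potentially misleading statement about trial validity.

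**What to change.** Replace the sentence with text to this effect: *Baseline characteristics will be summarized by arm (mean and SD, or number and percentage) without significance tests, and relevant differences will be described by their size. Whether randomization was carried out correctly will be judged by comparing the allocations given, in order within each gender-by-relationship stratum, with the independent researcher's schedule.*

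In the same edit, reconcile the conditional correction for baseline scores. The tests are the only baseline comparison of the arms that the Statistical Analysis section specifies, so removing them leaves that condition without a criterion. Prespecify adjustment for the baseline score of each outcome regardless of observed imbalance.

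The cost is wording only: no new data, fewer tests, and a schedule that is already part of the design. The small downside is a baseline table without p values, which some readers expect.

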### Recruitment of Participants and Study Procedure

People will be recruited through different sources. First, Alzheimer Nederland (AN), the Dutch Alzheimer’s national association, will place announcements about the study on their website, social media pages, and newsletter, among other places. Second, study banners will be placed on other relevant websites. Third, the research team will leave brochures and posters while visiting Alzheimer’s cafés and memory clinics. All of our study announcements will refer to our study website [29], which contains information about the study purpose and procedures. Those who are interested in participating will be able to register through this study website. We will then contact them via email where we will include a brochure with the information and a link to the online battery of baseline questionnaires, which includes the screening questions and the online written informed consent form. At this stage, we will fully inform potential participants about the aim and procedures of the study and will again ask for online informed consent. Based on the answers to the screening questions from the battery of baseline questionnaires, we will check the inclusion and exclusion criteria. Those who do not fulfil our inclusion criteria or do not provide informed consent will not be able to continue to fill out the remainder questionnaires of the baseline battery. They will receive an automated message explaining why they cannot participate in the study. We will stress that they can consult their general practitioner and AN at any time. Those who fill out the full battery of baseline questionnaires and fulfil the inclusion criteria will be included in the study and will be randomized. The outcome of the randomization will be communicated to participants via email. Participants randomized to the iSupport group will receive the intervention log-in details and they will have access to the intervention for 3 months. After the third month, participants will no longer have access to the intervention. Those who are randomized to the waiting list control group will be informed that they will receive log-in details for iSupport after they have completed the 3-month assessment. They will be free to seek any help they want in the meantime. The postintervention measurement and follow-up measurement will be sent via email 3 months and 6 months after randomization, respectively.

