## Discussion

In this paper, we outlined the design of an RCT to examine the effectiveness of iSupport for families and other unpaid carers of people with dementia in improving their mental health and coping strategies.

iSupport was developed by the WHO for global implementation and therefore includes guidelines for translation and cultural adaptation of the intervention. Internet interventions are a promising channel to prevent or treat mental health conditions of relatives and other unpaid carers who face greater risk of experiencing mental health problems themselves [41]. iSupport may increase unpaid carers’ worldwide accessibility to the support they need through the internet. An advantage of the intervention is that it is flexible and carers can decide which lessons they want to complete. Another advantage is that it can be provided with no or minimal professional support. This enables upscaling of the intervention without high costs. It might fit into a stepped-care model, in which only the carers who need more support are stepped up to face-to-face interventions. Additionally, family and other unpaid carers go through different stages during the course of dementia; their needs and preferences for training and support may substantially vary accordingly [42,43]. iSupport contributes to enriching and completing a continuum of interventions addressing the needs of carers in the Netherlands. This continuum should cover interventions from face-to-face to online interventions as well as guided to self-help interventions and everything in between.

The fact that the intervention is offered with minimal support might not only be a strength but also a weakness. It might lead to higher dropout rates. A review on the treatment adherence of online interventions carried out in 2008 [44] shows that in some trials participants never accessed the interventions tested, while others used them inconsistently. We try to minimize that risk by providing personalized automated feedback in iSupport as well as via periodic contact with e-coaches and the option to consult the e-coach more frequently. Hopefully, this encourages carers to continue with the intervention.

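### The analysis plan does not commit to a primary analysis that is robust to dropout, and its only sensitivity analysis, in completers, cannot test the primary result if loss depends on the 3-month stress score

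*Protocol article*

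**What the plan says.** Everything decisive stands in the protocol article's Statistical Analysis section.

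- Principle: "The primary analyses will be based on the intention-to-treat principle".
- Primary model: "We will use the generalized estimating equation to examine the association between changes in stress scores" and treatment arm. No weighting, imputation or working correlation is given.
- Baseline: "We will correct for baseline scores if they are not equally distributed".
- Missing data: "Missing data handling will depend on the amount and pattern of missing data, selecting the most appropriate technique".
- Dropout check: "We will also check for differences between study dropouts and those who remain in the study at 3 months". No analysis is tied to the result.
- Sensitivity: "Sensitivity analyses will be performed only with those participants that filled out the pre- and posttest questionnaires (ie, completers"). No other sensitivity analysis is stated.
- Effect size: a Cohen d from the two posttest means and the pooled standard deviation.

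Two other places bear on how likely loss is. Recruitment of Participants and Study Procedure says waiting-list carers will be told that "they will receive log-in details for iSupport after they have completed the 3-month assessment"; carers in the iSupport arm lose access after month 3. The Discussion concedes that minimal support could raise dropout. Neither that section nor Sample Size gives a rate or an allowance.

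**The concern.** An unweighted GEE on available data is guaranteed in general only when data are missing completely at random. Here loss may well differ by arm: a control carer who answers T1 gains the programme, while an iSupport carer gains nothing further. If the iSupport carers who leave are also the more stressed ones, those still observed at T1 are a selected group.

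Three features of the plan then work together. Baseline PSS, which would absorb loss that depends on baseline stress, enters only if the arms look unequal. Randomisation tends to make all randomised carers look equal, so the rule will often leave baseline out. The missing-data technique is open. The one stated sensitivity analysis drops everyone without a posttest, so it assumes at least as much about the missing carers as the primary analysis does. At stake is the size of the primary effect, and a reader's ability to judge whether dropout could explain it.

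**Working it through.** **The plan's own figure.** With d = 0.40, two-sided alpha 0.05, power 0.80 and 1:1 allocation, the two-sample t test (noncentral t) needs 100 per arm (power 0.804). The stated 200 reproduces exactly, with complete data. The calculation therefore holds no loss assumption that could be used here.

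**Assumptions for the illustration (none is in the article except d = 0.40).** PSS in SD units, SD 1; correlation 0.5 between any two visits; true T1 effect -0.40 (negative means less stress); control loss 15% at random; iSupport loss by a logistic rule with log-odds rising 0.8 per SD of PSS, from an intercept near 30%.

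**Formulas.** Among iSupport carers still observed at T1, let *a* be the shift in mean baseline PSS and *b* the shift in mean T1 PSS caused by selective loss. Controls are lost at random, so they have no shift. Then:

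- raw posttest contrast, or arm-by-time GEE with independence correlation: -0.40 + b
- completer change contrast: -0.40 + b - a
- baseline-adjusted analysis, or GEE with the correct exchangeable correlation: -0.40 + b - 0.5a

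**Scenario 1: iSupport loss rises with baseline PSS.** Simulation gives a of about -0.22, at 30% to 32% loss. The T1 shift follows by regression: b = 0.5 × (-0.22) = -0.11.

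**Scenario 2: iSupport loss rises with the T1 score itself.** Simulation gives b of about -0.18, at about 26% loss. Then a = 0.5 × (-0.18) = -0.09.

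| T1 analysis | Scenario 1 | Scenario 2 |
|---|---|---|
| Raw posttest; independence GEE | -0.40 - 0.11 = -0.51 | -0.40 - 0.18 = -0.58 |
| Completer change | -0.40 - 0.11 + 0.22 = -0.29 | -0.40 - 0.18 + 0.09 = -0.49 |
| Exchangeable GEE; baseline-adjusted | -0.40 - 0.11 + 0.11 = -0.40 | -0.40 - 0.18 + 0.045 = -0.535 |

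Direct simulation of each analysis agrees with these to about 0.01. A steeper dependence on the T1 score (1.0 per SD), in a smaller run, gave -0.53 to -0.64 across the same analyses.

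**Reading the table.** In scenario 1, analyses that the section leaves open run from 0.11/0.40, about 28%, too small to about 28% too large on the same data. Conditioning on baseline brings the estimate back to the truth. In scenario 2 nothing does, and every analysis overstates the benefit. A completer result near the primary one would then look like confirmation.

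One further reading matters. If the GEE outcome is the change score itself, its available T1 data come from the same carers as the completer analysis. The two would then agree at about -0.29 in scenario 1 as well.

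**The case against.** The strongest reply is that the section fixes less than it is charged with. If the technique is still open, GEE after multiple imputation or with inverse-probability weights is not excluded, and both are valid under missing at random. The article is condensed, and naming the technique is often left to the full plan. This stands: the open technique alone would be no more than missing detail. A reader might infer that the trial has committed itself to an analysis valid only under missing completely at random. The text does not support that.

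Nor does it support the inference that the method will be chosen in the light of the treatment result. The choice is tied to the amount and pattern of missing data, which can be assessed with the arms masked.

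The figures also cut both ways. In scenario 1 an exchangeable GEE is essentially unbiased, the completer change contrast would visibly disagree with an arm-by-time GEE, and the planned comparison of dropouts and stayers could pick up the baseline difference. That is correct. It shows that the answer depends on a working correlation and a baseline rule that the article does not settle. None of these checks helps in scenario 2, where a mixed model on its own would do no better either.

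Finally, the evidence for heavy loss is thin. The review of online interventions that the Discussion cites, where "in some trials participants never accessed the interventions tested, while others used them inconsistently", concerns adherence; a non-user who answers T1 is fully counted under intention to treat. The incentive argument rests on one section. The Abstract, Study Design and the waiting-list section describe control access by time alone. So dropout is a risk that the article raises, not one it predicts.

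**Conclusion.** The concern holds in a limited form. The stated combination (GEE, baseline correction only on imbalance, missing-data handling left open, completers as the only sensitivity analysis) does not commit the trial to a primary analysis that withstands loss related to baseline stress. It also contains no analysis that probes loss related to the T1 score.

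Under the assumed 30% against 15% loss, the available estimates run from -0.29 to -0.51 around a true -0.40 when loss follows baseline PSS, and from -0.49 to -0.58 when it follows T1 PSS. These are illustrations that rest on the assumed rates, slopes and correlation of 0.5. With loss unrelated to stress, all the analyses are unbiased. It would go too far to say that the primary estimate will be biased by some 28%: the article gives no dropout rate and nothing that ties loss to stress. The plan should be changed, because the improvement is concrete and cheap.

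**What to change.** Before data lock:

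1. Name one primary analysis that is valid under missing at random and always includes baseline PSS. Either a likelihood-based mixed model on all randomised carers (PSS at T0, T1 and T2, arm by time), or GEE after multiple imputation by arm using the baseline scales already collected (PSS, CES-D, HADS-A, ZBI). Remove the rule that corrects for baseline only on imbalance.
2. Make a delta-adjusted (tipping-point) analysis of missing T1 PSS the main sensitivity analysis: impute under missing at random, worsen the imputed iSupport scores in steps, and report the step at which the conclusion changes.
3. Keep the completer analysis as supplementary at most.

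The details of item 1 are one acceptable choice among several; what matters is that one is fixed. Loss by arm should already appear in the planned CONSORT diagram. The cost is a little more analysis work and no new data.

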**Methods:**

A superiority two-arm RCT comparing the effects of the online support program with a waiting list control condition will be carried out in the Netherlands. The iSupport intervention was developed by the World Health Organization and is based on cognitive behavioral therapy principles. It has five main themes divided into 23 lessons. Carers can pick and choose which lessons they want to complete. We aim to recruit 200 unpaid carers. The experimental group (n=100) will be provided with access to the intervention for 3 months following randomization; those in the waiting list control group (n=100) will be granted access to the intervention after 3 months. Assessments will be conducted at baseline (T0), 3 months after baseline (post intervention, T1), and 6 months after baseline (follow-up, T2). The primary outcome is perceived stress, measured by the Perceived Stress Scale. Secondary outcomes are symptoms of depression and anxiety, caregiver burden, sense of competence, self-efficacy, mastery, and carers’ attitudes toward dementia and their person-centered approach (ie, to what extent carers tailor the provided care to the interest, needs, and history of the person with dementia).

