### Inclusion and Exclusion Criteria

The potential participants will be relatives or other unpaid carers of people with dementia. The participants must be at least 18 years old. We will focus on unpaid carers who are providing care to a family member, friend, or neighbor for at least 6 months, regardless of the number of hours per day they spend on care provision. To be included in the study, their well-being will need to have been affected at least to some extent. We will measure well-being via levels of stress, existence of depressive or anxiety symptoms, or experience of caregiver burden. This means that the carers will need to have a score greater than 13 on the Perceived Stress Scale (PSS) [25], a score of 4 or greater on the Hospital Anxiety and Depression Scale-Anxiety subscale (HADS-A) [26], or a score of 4 or greater on the Centre for Epidemiological Studies Depression scale (CES-D) [27]. Caregiver burden will be assessed using a one-item scale with a score ranging from 1 (no burden) to 10 (extreme burden); people will be eligible for the study if they scored 4 or greater.

Furthermore, there needs to be an indication that the person that is being cared for is indeed living with dementia. Therefore, carers will have to fill out the Ascertain Dementia 8-item informant questionnaire (AD8) [28]. The AD8 assesses the functional decline of the person with dementia attributed to cognitive impairment over the past years as reported by the carer. In order to be included, the score needs to be 2 or higher. This cutoff has been shown to have a good discriminative validity between people with and without dementia. We will also ask whether or not the person has been officially diagnosed with dementia, but this will not serve as an inclusion criterion.

We will exclude people who are unable to comprehend written Dutch or have no access to the internet. If both groups differ regarding the professional support they have received, we can control for it in the analyses, but receiving professional support will be not be used as an exclusion criterion.

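### Baseline stress score is adjusted for only if the arms look unequal at baseline: the primary model is chosen from the data and precision is lost

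*Protocol article*

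**What the plan says.** All points are in the protocol article.

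- Statistical Analysis opens with a check on randomisation: "We will first check whether or not the randomization was successful by comparing the two groups for all baseline variables", using t tests or chi-square tests.
- The primary model follows: "We will use the generalized estimating equation to examine the association between changes in stress scores (ie, PSS scores) and treatment arms".
- The adjustment rule is then: "We will correct for baseline scores if they are not equally distributed". The section does not say what counts as unequal. The same analyses are to be repeated for burden, anxiety and depression, sense of competence, self-efficacy and mastery.
- Cohen d is reported afterwards and "is the difference between the two posttest means divided by the pooled standard deviation".
- Perceived stress is measured at all three assessments, so the baseline score is available for everyone randomised.
- Randomization and Blinding stratifies on gender and relationship. Baseline stress is not a stratification factor, so it can differ between arms by chance.

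No other section commits to including the baseline score in all cases.

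**The concern.** With concealed computer-generated 1:1 allocation, any baseline difference between arms is due to chance. Testing it does not show whether adjustment is worthwhile. That depends on how strongly the baseline score predicts the later score, and the baseline Perceived Stress Scale (PSS) score is the same instrument as the outcome.

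The rule has two consequences. First, the form of the primary model is left open until the data are in, because no threshold is fixed. Second, in most trials the covariate would be left out, so precision is forgone and imbalances too small to trip the rule stay in the estimate.

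**Working it through.** **Inputs from the protocol article (Sample Size; Randomization and Blinding).** d=0.40, two-sided alpha .05, power .80, 100 per arm, 1:1 allocation.

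**Assumptions not in the document.** A trigger of p<.05 on the baseline t test; T0-T1 correlation r from 0.3 to 0.7; SD of 1 on the standardised scale; complete data.

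**1. The plan's own figure.** The exact two-sample t test needs 100 per arm for d=0.40, with power 0.804. The normal approximation gives 99 per arm, and power at 100 per arm of Φ(0.40/√(2/100) − 1.96) = Φ(0.868) = 0.807. The stated 200 is reproduced, as an unadjusted comparison.

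**2. Power with a fixed analysis.** Replace the SD of 1 by √(1−r²) when baseline is a covariate, or by √(2(1−r)) for an unadjusted change score.

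- r=0.5, covariate: SD 0.866; Φ(2.828/0.866 − 1.96) = Φ(1.306) = 0.904. Only 74 per arm would be needed for 80% power.
- r=0.5, change score: SD 1.000; power 0.807.
- r=0.3: covariate 0.843, change score 0.667.
- r=0.7: covariate 0.977, change score 0.955.
- Unadjusted posttest: 0.807 at every r.

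**3. Power of the conditional rule.** Simulated with at least 20,000 trials per setting, adjusting only when the baseline test has p<.05. Adjustment was triggered in about 5% of trials. The generalized estimating equation can be read as modelling posttest scores or change, so both are shown.

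| r | Always adjust | Rule, posttest reading | Rule, change reading |
|---|---|---|---|
| 0.3 | 0.833 | 0.801 | 0.674 |
| 0.4 | 0.86-0.87 | 0.81-0.82 | 0.74 |
| 0.5 | 0.901 | 0.814 | 0.818 |
| 0.6 | 0.94 | 0.82 | 0.89 |
| 0.7 | 0.976 | 0.825 | 0.957 |

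**4. Type I error of the rule (d=0; r = 0.3, 0.5, 0.7).** 0.036 to 0.047 on the posttest reading and 0.039 to 0.046 on the change reading: slightly below nominal.

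**5. Imbalance that escapes the trigger.** The largest non-significant baseline difference is t(.975; 198) × √(2/100) = 1.972 × 0.1414 = 0.279 SD.

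- Posttest reading: the estimate shifts by r × 0.279, that is 0.08, 0.14 or 0.20 SD at r = 0.3, 0.5 or 0.7.
- Change reading: it shifts by (1−r) × 0.279 in the opposite direction, that is 0.20, 0.14 or 0.08 SD.
- At r=0.5, 0.14/0.40 = 35% of the planned effect. This is the extreme case; a typical chance imbalance is smaller.

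**The case against.** The strongest reply is that the primary model concerns changes in stress, so baseline may already enter every analysis by subtraction. The conditional sentence would then govern only an additional covariate term. This is fair. A reader might infer that baseline stress is ignored in about 95% of trials, but the text does not support that: it holds only on the posttest reading, and the 5% rests on an assumed trigger. On the change reading the loss is about 2 points at r=0.7. It does not disappear, though, and it grows to about 16 points at r=0.3 (0.833 versus 0.674).

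Other stronger readings also fail:

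- *The trial is underpowered or its sample size is wrong.* The size was set for an unadjusted test and is right for one. At r=0.5 the conditional rule still gives 0.81 to 0.82. Power falls clearly below 0.80 only on the change reading with r below about 0.5.
- *The result is biased or false positives are inflated.* Averaged over randomisations the estimate is unbiased, and the rule is conservative.
- *Many baseline tests make chance adjustment likely.* Only baseline scores trigger correction; a chance difference in, say, education triggers nothing under the quoted sentence.
- *Cohen d is wrong.* A raw posttest d is a conventional descriptive summary, given after the main model.
- *Controlling for professional support would bias the effect.* The sentence "If both groups differ regarding the professional support they have received, we can control for it in the analyses" stands in the eligibility section and is permissive. It most naturally refers to support at entry, and the table of measures lists no measure of professional support after randomisation.

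**Conclusion.** The point stands as a free improvement. The plan fixes a data-dependent covariate rule with no stated threshold, and always including baseline gave higher power at every correlation examined. At r=0.5 the gain is 8 to 9 points. From r=0.3 to r=0.7 it ranges from about 2 to about 16 points, depending on r and on whether the model analyses posttest scores or change.

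The residual imbalance is chance error within the trial at hand, up to about 0.14 SD at r=0.5. These sizes rest on the assumed p<.05 trigger, the assumed correlation and complete data. The conclusion that the rule should go does not depend on the exact values.

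**What to change.** Replace the conditional sentence with: *The baseline value of the outcome is included in every model (as a covariate, or through a longitudinal model with a common baseline mean), regardless of observed imbalance.* Apply it to the primary outcome and to each secondary outcome analysed in the same way.

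Drop the baseline significance tests as a trigger for adjustment; a descriptive baseline table is enough. Preferably, also report the standardised effect from the baseline-adjusted T1 difference alongside the raw Cohen d.

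The cost is wording only. The baseline scores are already collected from everyone randomised, and the sample size need not change.
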